## Abstract

**Background:**

The legacy of the Soviet childcare system has contributed to persistently high rates of child institutionalization across many countries in Eastern Europe, the Caucasus and Central Asia. Although countries throughout the region have adopted deinstitutionalization and family reunification policies, most programs provide limited support to address children’s mental health needs or family functioning during the critical transition from institutional care to family and community reintegration.

**Objective:**

This study compares and optimizes 3 prevention and early intervention approaches to improve mental health outcomes for children with a history of institutional care. Using the multiphase optimization strategy, the study experimentally evaluates which interventions—family strengthening, trauma-focused child mental health services, or economic empowerment—yield meaningful improvements in child mental health.

**Methods:**

This randomized clinical trial used a full 2³ (2×2×2) factorial design. A total of 439 children aged 7 to 12 years with a history of institutional placement and subsequent family reunification, along with 305 primary caregivers (parents or kin caregivers), were recruited from the 3 largest cities in Azerbaijan. Participants were randomly assigned to 1 of 8 experimental conditions, each receiving different combinations of the 3 interventions plus usual care. The family strengthening intervention consisted of a 12-session multifamily group program designed to improve parent-child relationships and supportive parenting. The asset-based economic empowerment intervention included opening a Matched Child Development Account with a US $50 seed deposit, 2:1 matched savings up to US $20 per month, and an 8-week financial education program for caregivers and children. Data on child mental health outcomes (self-esteem, depression, posttraumatic stress disorder, attention-deficit/hyperactivity disorder, internalizing and externalizing problems), cognitive and social processes (executive functioning, working memory), social and academic functioning (eg, grades), family functioning, and economic well-being were collected at baseline, 1-year, and 2-year follow-ups using multi-informant surveys (child, caregiver, and teacher reports), digital cognitive tasks (Wechsler Intelligence Scale for Children, Fifth Edition and Cambridge Neuropsychological Test Automated Battery), and clinical assessments.

**Results:**

Recruitment occurred between 2022 and 2023, with 2-year follow-up data collection completed in 2025. Intervention effects analyses are ongoing and are expected to be completed in 2026.

**Conclusions:**

This study will identify the most effective and efficient combination of interventions to support the mental health of children reintegrating from institutional care. The findings are expected to provide important evidence to support deinstitutionalization and family reunification initiatives in the region and strengthen the global evidence base on effective, scalable community-based interventions addressing multilevel determinants of mental health among at-risk children in low- and middle-income countries.

## Introduction

The region of Eastern Europe and Central Asia has the second-highest rate of children living in institutional care worldwide: 232 per 100,000 compared to a global average of 105 per 100,000 [1]. Due to the economic crisis following the collapse of the Soviet Union, many countries in the region hosted a population of “social orphans,” children who have at least one living parent but were voluntarily placed in institutions due to socioeconomic reasons (eg, poverty, divorce, labor migration) [2]. The experience of institutionalization can put children at high risk for social, emotional, and behavioral difficulties due to social isolation, deprivation, a high child-to-service provider ratio [3-5], and the trauma of separation from their family [6,7].

Acknowledging the detrimental effects of institutionalization, Azerbaijan and many other countries in the region have implemented national deinstitutionalization programs aimed at closing institutions and reunifying children with their families of origin [6,8]. These programs typically provide case management but do not offer support during reunification to address children’s mental health needs, family functioning, or parental distress [9]. Furthermore, most deinstitutionalization programs do not address family-level poverty, which often spurred initial institutional placement, creating a risk of poor psychosocial outcomes associated with economic precarity.

Prevention and early intervention reduce children’s risk of developing mental health disorders in adulthood, improve integration into society, and concurrently impact a number of psychosocial outcomes [10-12]. Yet, there are no evidence-based, culturally tailored, preventive mental health interventions available for institutionalized children in Azerbaijan and other countries in the region. Existing interventions, primarily formulated in high-resource countries, such as the United States, require highly skilled clinicians and are not adapted for developing countries with limited financial and mental health resources [13,14]. Using innovative research methodologies to develop early prevention programs is essential to optimize the well-being of reunifying children and families in low- and middle-income countries (LMICs) such as Azerbaijan.

This paper describes a study protocol for a US National Institute of Child Health and Human Development/NICHD (R01-HD099847) study titled “Optimizing prevention approaches for children reintegrating from orphanages in Azerbaijan.” The study is registered with the ClinicalTrials.gov registry (NCT05396625). Trial registration was completed on May 19, 2022, and the recruitment start date was May 1, 2022; therefore, the trial was registered shortly after recruitment had begun and was not prospectively registered.

Although recruitment and data collection have been completed, this protocol paper documents the study design, intervention components, measurement approach, ethical safeguards, and prespecified analytic plan prior to the publication of the main trial findings. No intervention effects or primary outcome results have yet been published. Baseline characteristics are reported solely to describe the enrolled sample and assess comparability across randomized conditions, not as evidence of intervention effectiveness.

## Methods

### Study Design

This randomized clinical trial used a full 2³ (2×2×2) factorial design based on the multiphase optimization strategy (MOST) framework to test and compare three intervention approaches: (1) a family-strengthening intervention, (2) trauma-focused child mental health services, and (3) asset-based economic empowerment via Child Development Accounts (CDAs).

Multicomponent interventions are often tested as “bundles,” making it difficult to disentangle the contributions of individual components. The MOST is a systematic method that allows for the testing of the independent effects of different intervention components to identify their most optimal combination [15]. While multiarm randomized controlled trials are costly, often limited in arms, and require larger sample sizes, the MOST uses a factorial design. By comparing combinations of experimental conditions, the study can have a greater number of conditions without a substantial increase in sample size. This is advantageous in LMICs, where it is essential to implement only the most efficacious aspects of a program. The MOST consists of three phases: (1) preparation, (2) optimization, and (3) evaluation of the optimized intervention in a randomized controlled trial [16]. This study falls within the optimization phase.

This study includes 3 factors—the intervention approaches—each with 2 levels (delivered/“on” or not delivered/“off”). This is a full 2×2×2 factorial design, meaning that the study has 8 different experimental conditions or groups (2^3^=8) [17]. Child-parent dyads (n=439) were randomly assigned to 1 of 8 groups (about 54 dyads per group), which determined the combination of interventions they received. Given this design, half of the sample (n≈220) received each intervention (eg, families assigned to groups 1‐4 received the family-strengthening intervention and were compared with families from groups 5‐8; Table 1).

**Table 1. T1:** Experimental conditions^a^.

Group	Usual care	Experimental interventions		
	Standard deinstitutionalization program	Family strengthening	Trauma-focused mental health services	Economic empowerment
1	On	On	On	On
2	On	On	On	Off
3	On	On	Off	On
4	On	On	Off	Off
5	On	Off	On	On
6	On	Off	On	Off
7	On	Off	Off	On
8	On	Off	Off	Off

a Child-parent dyads (n=439) are randomly assigned to 1 of 8 experimental conditions (~54 dyads per group), determining how many and which intervention components participants receive.

### Objectives

This trial has three study aims:

To refine, test, and compare the effects of 3 interventions (family-strengthening intervention, mental health services, and economic intervention) on mental health outcomes (eg, posttraumatic symptoms, depression, anxiety, internalizing and externalizing problems) and cognitive functioning (eg, working memory, executive functioning, impulsivity) among 7‐ to 12-year-old children with a history of institutional care in Azerbaijan.To examine the role of hypothesized intervention mediators (eg, emotion regulation, supportive parenting, parental stress) and moderators (eg, child’s and caregiver’s age, gender, length of time in institution, family structure, intervention adherence) in improving child mental health outcomes.To explore the facilitating factors and barriers to the implementation and participation in each intervention component using qualitative interviews with participants and service providers.

The study also aims to conduct a secondary analysis to estimate the preliminary costs (operations and personnel) of each intervention component relative to usual care alone.

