### Intervention Quality Assurance and Implementation Measures

For each component, we will analyze data regarding participation (eligibility, enrollment, and attrition rates), intervention fidelity (via facilitator and participant rating forms completed at the end of each session), safety (number of adverse events), intervention acceptability (participant satisfaction, session attendance, and associations between satisfaction and attendance), perceived usefulness (relevance and utility), and cross-arm contamination.

Two interim analyses will be conducted when 33.3% and 66.7% of the planned sample size have completed 6-month follow-up assessments. With respect to efficacy, if any interim analysis shows statistical significance (*P*<.05) for all primary outcomes, the study will be stopped, indicating a significant benefit of 1 intervention over another. With respect to futility, if the effect size estimates suggest a null result is likely given the planned total sample size, the study may be stopped to conserve resources. A post hoc power analysis will assess the minimum sample size needed to achieve 80% power *and* reject the null hypothesis at each interim analysis. If this exceeds the planned 400 dyads for self-reported outcomes, the investigative team will discuss whether to stop the study for futility or modify the design to avoid it, such as increasing enrollment or hiring additional staff.

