Aim 1: To estimate the effects of intervention components on child mental health outcomes, differences in outcomes (eg, depression score) will be tested across 3 time points (baseline, 1 year, and 2 years), under an intent-to-treat basis, using linear mixed models. This approach accounts for the autocorrelation of observations nested within individuals over time. We will use logistic functions for binary outcomes (eg, mental health symptoms above the clinical cutoff), Poisson or negative binomial functions for count outcomes (eg, the number of aggressive behaviors), and linear functions for continuous variables (eg, self-esteem score). Statistical inference will be based on F-statistics and their associated *P* values for between-subject effects (the intervention assignment × time terms). To estimate the main effects for the 3 intervention components, we will determine if there is a difference in change across time using the baseline as the reference point (eg, 1 year vs baseline; 2 years vs baseline). We will also include 2-way interactions between components (eg, Family Strengthening by Economic Empowerment by Time interaction). Since we will use effect (–1, 1) coding rather than dummy (0, 1) coding, the power for tests of main effects and interactions will be identical for similarly sized effects. Covariates will include baseline attributes for outcome variables (eg, child’s age and gender, caregiver characteristics).Aim 2: To test which intervention component is mediated by hypothesized mediators, including (1) supportive parenting (eg, quality of child-parent relationships), (2) emotion regulation (eg, self-regulation), and (3) parental stress (eg, stress response). We will use a 2-step process [61] to test (1) a measurement model using confirmatory factor analysis that examines the relationships between the latent constructs and their indicator variables and (2) a structural model to test the hypothesized relationships between the latent mediating and outcome constructs and the intervention [62]. We will use the maximum likelihood method of parameter estimation with missing data. We will also conduct separate analyses to examine the effectiveness of intervention components in specific subgroups (eg, by gender).Aim 3: Qualitative analysis will be conducted in both Azerbaijani and English to explore barriers and facilitators to intervention participation and implementation. Bilingual investigators and 2 additional coders will independently review interview transcripts and conduct thematic analysis [63] and content analysis [64] using Dedoose [65]. Analyses will assess themes and concepts regarding participants’ and intervention facilitators’ perspectives on mental health needs, intervention engagement and acceptability, changes in family relationships and dynamics, and contextual and sociocultural factors influencing intervention delivery and outcomes.

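### Aim 1 and the interim rule speak of one intervention against another, but the stated tests set each component only against its own absence

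*Protocol article*

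**What the plan says.** **The comparison promised.** The Abstract (Objective) opens with "This study compares and optimizes 3 prevention and early intervention approaches". Study Design also describes testing and comparing three approaches, and Objectives gives Aim 1 as "To refine, test, and compare the effects of 3 interventions".

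**The interim conclusion.** Under Intervention Quality Assurance and Implementation Measures, if P<.05 is reached for all primary outcomes at an interim look, "the study will be stopped, indicating a significant benefit of 1 intervention over another".

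**The tests stated.** In Study Design, families in groups 1 to 4 "received the family-strengthening intervention and were compared with families from groups" 5 to 8, which is family strengthening on versus off. Analytical Strategy, Aim 1, says "To estimate the main effects for the 3 intervention components, we will determine if there is a difference in change across time", with baseline as reference. It adds "Statistical inference will be based on F-statistics and their associated" P values for the assignment-by-time terms, and then "We will also include 2-way interactions between components". A later paragraph of that section adds Benjamini-Hochberg control. No contrast between two component effects is described.

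**The hypothesis.** The Discussion states it as one or more of the three interventions improving outcomes at 1 and 2 years.

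**The concern.** A significant on/off effect shows that a component does better than its own absence. It says nothing about how that component compares with a different one. A two-way interaction asks whether one component's effect depends on another being present, which is not a ranking either. The interim sentence therefore attaches a conclusion to a test that cannot deliver it, and the comparison named in Aim 1 has no stated test.

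What is at stake is what the trial may conclude. With no stated between-component estimate, a reader told that the trial compares interventions may take a significant component to be better than a non-significant one. Two components with the same true effect can easily differ in that respect by chance.

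**Working it through.** **Inputs.** From Power Calculations: two-sided alpha 0.05, power 0.80, 360 children analysed (180 per level) after 10% attrition from 400, and detectable effect sizes of 0.09 to 0.12. From Analytical Strategy: three time points and effect (−1, 1) coding. Assumed, because the article does not give them: the effect-size metric (Cohen's f) and the autocorrelations (0.1 and 0.5).

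**1. The plan's own figures.** 360 / (1 − 0.10) = 400, as stated. For a two-group (on/off) between-factor repeated-measures test, the noncentrality is λ = f² × N × m / (1 + (m − 1)ρ), with N = 360 and m = 3. Solving for 80% power gives f = 0.094 at ρ = 0.1 and f = 0.121 at ρ = 0.5, which matches 0.09 to 0.12. The match is not unique. An eight-group group-by-time test gives 0.125 to 0.093 over the same two ρ values, so the range is consistent with an on/off calculation but does not prove it.

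**2. Split verdicts when true effects are equal.** In a balanced 2×2×2 design with effect coding the component estimates are uncorrelated, so the tests are treated as independent. With power p for each:

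- Two components, exactly one significant: 2p(1 − p).
- Three components, verdicts not all alike: 1 − p³ − (1 − p)³.

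| Power per test | Two split | Three mixed |
|---|---|---|
| 0.5 | 50% | 75% |
| 0.8 | 32% | 48% |
| 0.9 | 18% | 27% |

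For p = 0.8: 2 × 0.8 × 0.2 = 0.32, and 1 − 0.512 − 0.008 = 0.48. A simulation of 20,000 trials with N = 360, one continuous outcome and an effect-coded model including the two-way interactions gave 32.4% and 48.6%. In the same trials the direct A−B contrast rejected in 4.6%, close to its nominal 5%.

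**3. Precision of a direct contrast.** Var(A − B) = Var(A) + Var(B) = 2 Var(A), so SE(A − B) = √2 × SE(A) = 1.41 × SE(A). If a single component effect has 80% power, a between-component difference of the same size has power Φ((1.960 + 0.842)/1.414 − 1.960) = Φ(0.021) = 0.508. The simulation gave 50.7%. For 80% power, the difference must be 1.41 times as large (f about 0.094 × 1.41 = 0.13 to 0.121 × 1.41 = 0.17), or the analysed sample must be doubled (2 × 360 = 720).

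**The case against.** The strongest reply is that on/off main effects are the standard way to screen components in a factorial optimization trial. Components can be kept together in a package, so choosing a package does not require showing that A beats B. On this view Study Design already defines the comparison as on versus off, and the Discussion hypothesis is answered by the planned tests. All of that stands: neither the design nor the component tests are at fault.

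A reader might infer that the trial will rank or select components by which ones reach significance. The article does not say so. It states no selection rule, the mixed model yields effect estimates, and component costs are also to be estimated. The 32% and 48% therefore measure a risk of misreading, not a planned procedure. They also assume equal effects, one outcome and unadjusted alpha. The article says that power is set by the component with the smallest effect; if the other components have higher power, the split rates change.

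It can also be said that contrasts may sit in an analysis plan not shown. For that reason their absence is not the point. The point is that the article's wording claims more than its stated tests support, and the interim sentence would remain wrong whatever another document contains.

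Finally, recruitment and follow-up are complete, so correcting the interim sentence changes no stopping decision. That is true. It changes interpretation only.

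**Conclusion.** The mismatch is real but limited. The interim sentence draws a between-intervention conclusion from tests that do not address one, and the verb compare in Aim 1 has no matching test. The on/off tests remain valid for the Discussion hypothesis.

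If significance verdicts were used as a ranking, equal components would look different in about 32% of trials (two components) or 48% (three) at 80% power, against about 5% for a direct contrast of two. These figures assume a balanced design, independent tests, independent children and unadjusted alpha. Sibling clustering would lower power for both kinds of test but would leave the 1.41 ratio unchanged.

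The correction is worth making because the article reports the effect analyses as still ongoing and unpublished.

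**What to change.** 1. **Intervention Quality Assurance and Implementation Measures:** replace the closing phrase of the efficacy sentence with *benefit of a component versus its absence*.
2. **Objectives and Analytical Strategy, Aim 1:** choose one of two routes.
   - Report the pairwise differences between component-by-time coefficients (A−B, A−C, B−C) from the same mixed model, with 95% confidence intervals. Present them as secondary estimates outside the primary Benjamini-Hochberg family, labelled with the date they were specified.
   - Or reword Aim 1 as *estimate the effect of each component versus its absence*.
3. **Under either route:** state that no component will be called better than another because one is significant and the other is not.

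**Cost.** The first route needs only linear combinations from a model already planned; the second needs only wording. Keeping the contrasts outside the primary family matters. Three contrasts at two visits for seven outcome-informant measures (three child-reported, plus ADHD symptoms and social-emotional functioning from caregiver and teacher; clinician scale excluded) would add 3 × 2 × 7 = 42 tests and could shift the thresholds for the main component tests. The downside of the first route is precision: with about 51% power for a difference equal to the single-component detectable effect, many comparisons will be inconclusive and should be reported as such.

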### Power Calculations

Power calculations were conducted using the G*Power software [18,19]. To account for the repeated-measures design, power estimates were modeled across a range of effect sizes at 2 assumed autocorrelation values (ρ). Analyses were performed for a 2-tailed test with a type 1 error rate of 0.05 and desired power of 0.80, assuming a final analyzed sample size of 360 child participants (180 participants per intervention type) after a projected 10% attrition from an initial planned sample of 400 child participants (200 participants per intervention type). The results indicate that for continuous outcomes, 80% power is achieved for effect sizes between 0.09 and 0.12. The study is sufficiently powered to detect small-to-medium effects [20] for continuous outcomes over the entire follow-up period. In the MOST design, the study is powered based on the intervention component with the smallest effect size—in this case, the family-strengthening component.

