### Intervention B: Mental Health Services

Families were connected to clinicians from the NMHC to receive child mental health services. Services included a clinical assessment performed by a psychiatrist, the development of an individual care plan, and assignment to a mental health clinician—typically a child psychologist—who provided services to the child and caregiver. The trauma-focused child mental health services were grounded in the Attachment, Regulation, and Competency framework [36]. All clinicians delivering this intervention received additional training in trauma-focused mental health approaches, including Attachment, Regulation, and Competency, and participated in biweekly group supervision delivered by a bilingual licensed psychologist from the United States. The clinicians delivering this intervention were not involved in conducting research activities. As a public entity, the NMHC provides all mental health services to the public free of charge. Children typically attended individual sessions once a week (30‐45 min), with parent or caregiver involvement incorporated as clinically indicated. Up to 12 sessions were offered; however, services could be extended based on individual treatment plans and clinical needs.

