Child-parent relationship	
Brief Family Relationship Scale; Multidimensional Scale of Perceived Social Support	Child, caregiver
Parenting skills and practices	
Parenting Styles and Dimensions Questionnaire; Child Discipline	Caregiver, child
Parental distress	
21-item Depression Anxiety Stress Scale; Brief COPE	Caregiver
Socioeconomic deprivation, savings, and assets	
The rate of savings, asset accumulation, employment, type and stability of housing, financial security, and attitudes to saving and income-generating activities	Caregiver, admin records (bank statements)
Moderators	
Child’s sociodemographics	
Sociodemographic questionnaire (child’s age, gender, birth order)	Child, caregiver
Parent and family characteristics	
Sociodemographic questionnaire (parent’s gender, age, marital status, employment status, family size, family structure)	Caregiver
Parent	
Adverse Childhood Experiences International Questionnaire	Caregiver
Service use	
Types of services, the number of sessions attended	Admin records

a This table outlines outcomes, mediator, and moderators of interest.

Additional child-reported measures include social support (24-item Social Support Scale for Children) [48] and parental discipline (11-item Child Discipline Index) [49]. Child cognitive functioning was assessed using selected measures from the Wechsler Intelligence Scale for Children, Fifth Edition (WISC-V) [50] and the Cambridge Neuropsychological Test Automated Battery (CANTAB) [51]. WISC-V measures included Block Design, which assesses visuospatial reasoning and problem-solving abilities, and Picture Span, which evaluates visual working memory. CANTAB measures included the Emotional Bias Task, which assesses emotional processing and interpretation bias; the Motor Screening Task, which evaluates sensorimotor function and task comprehension; Reaction Time, which measures processing speed and attention; the Stockings of Cambridge, which assesses executive functioning and planning; and Spatial Span, which measures visuospatial working memory capacity.

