### Data Collection

Children, their caregivers, and their teachers completed surveys at baseline, year-1, and year-2 follow-up. Child and caregiver data were collected through interviewer-administered surveys conducted separately in Azerbaijani by trained graduate-level psychology students serving as RAs. Assessments were conducted at local field offices using iPads and the cloud-based Qualtrics survey platform and required approximately 50 to 60 minutes to complete. Teacher surveys were completed independently. All surveys contained the same scales, except for demographic data that do not vary over time (eg, ethnicity, age). Except for nonverbal digital cognitive tasks (WISC and CANTAB), all instruments were translated into Azerbaijani and tested in a pilot feasibility study. The CANTAB battery consists of simple computer-administered nonlinguistic tasks considered highly precise and largely independent of cultural and language differences [58].

Intervention participation and utilization data (eg, attendance, session completion, and types of services received) were collected from intervention administrative records. Information about children’s academic performance (eg, grades) was collected from school records.

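### Aim 2 lists adherence and sessions attended as moderators, but both arise after randomisation, so analysing them that way can produce false effect modification in either direction

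*Protocol article*

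**What the plan says.** In the Objectives, Aim 2 names its moderators in one list that runs from child and caregiver age and gender to "length of time in institution, family structure, intervention adherence". Table 2 (Outcome Measures) repeats the classification: under its Moderators heading it has a service-use entry, "Types of services, the number of sessions attended", taken from administrative records.

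Data Collection shows when these values arise: "Intervention participation and utilization data (eg, attendance, session completion, and types of services received) were collected from intervention administrative records". Table 1 shows that each component is off in four of the eight conditions. Under Intervention B, up to 12 sessions were offered, but "services could be extended based on individual treatment plans and clinical needs".

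On the method for effect modification, the Aim 2 paragraph of the Analytical Strategy says: "We will also conduct separate analyses to examine the effectiveness of intervention components in specific subgroups (eg, by gender"). It names no interaction between a component and a moderator. The interactions that the section does name, under Aim 1, are between components and with time. Aim 1 is analysed "under an intent-to-treat basis, using linear mixed models".

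**The concern.** A moderator in a randomised trial is a characteristic fixed before assignment, so that on and off can be compared within each of its levels. Adherence to a component is not such a characteristic. Children with the component off have no sessions of it to attend, so no off group exists at high or low adherence. An interaction of component with adherence then reduces to comparing high with low attenders inside the on arm, or each of them with the whole off arm. Both comparisons are between self-selected groups.

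The article gives grounds to expect that selection is related to outcome. Extra mental health sessions may go to children with greater need, which would make high attendance look harmful. Families are paid US $10 per session attended (Ethical Considerations), and the baseline results link economic deprivation to child internalizing problems, so attendance could track hardship. Better-organised families may also attend more and do better anyway. At stake is an Aim 2 result that reads as a dose effect or differential benefit when it reflects only who attended.

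**Working it through.** **Inputs from the documents.** Power Calculations: a "2-tailed test with a type 1 error rate of 0.05 and desired power of 0.80" and a "final analyzed sample size of 360 child participants (180 participants per intervention type"), so 180 on against 180 off for each component. The attrition step reproduces: 400 × 0.90 = 360. The detectable range of 0.09 to 0.12 cannot be confirmed, because its metric and the two autocorrelation values are not given; nothing below uses it. The article gives no figure for moderation and none for adherence.

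**Assumptions.** One follow-up outcome with SD 1; the same true effect in every child; adherence split at its median within the on arm (90 and 90); correlation r between adherence propensity and the untreated outcome, varied because the documents do not give it; family clustering ignored.

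**Bias.** With a median split, the mean untreated outcome is shifted by r × √(2/π) = 0.798r in high adherers and by −0.798r in low adherers. The false gap is therefore 1.596r. Its standard error is √[(1 − 0.637r²) × 2/90].

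- r = 0.1: gap 0.160, SE 0.149, ratio 1.07; probability of a significant gap 0.19.
- r = 0.2: gap 0.319, SE 0.147, ratio 2.17; P(Z > 1.96 − 2.17) = 0.58.

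A simulation of 4,000 trials per setting agrees. The false-finding rates hardly change with the true effect:

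| r | False high-versus-low finding | Apparent effect, high | Apparent effect, low (true effect 0.20 SD in all) |
|---|---|---|---|
| 0 | about 6% | 0.20 | 0.20 |
| 0.1 | about 19% | 0.28 | 0.12 |
| 0.2 | about 58% | 0.36 | 0.04 |
| 0.3 | about 90% | 0.44 | −0.04 |

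A negative r gives the mirror image, with low adherers appearing to benefit more. For scale, the single-wave difference detectable with 180 against 180 is (1.96 + 0.84) × √(2/180) = 0.295 SD, again without clustering. A shift of 0.16 SD in each half, at r = 0.2, is about half of that.

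**Baseline subgroups.** This part applies only if significance were compared between subgroups. With 80% power overall and equal halves, the noncentrality in each half is 2.80/√2 = 1.98 and the power 0.508. With an identical effect in both halves, exactly one is significant with probability 2 × 0.508 × 0.492 = 0.50. With no effect at all, it is 2 × 0.05 × 0.95 = 0.095. An interaction test holds the false-positive rate at 5%. Its power for a subgroup difference as large as the detectable main effect is Φ(2.80/2 − 1.96) = Φ(−0.56), about 0.29.

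**The case against.** The strongest objection is that the article states no model for adherence. The analysis plan, not shown, may use a sound method under a loose label, and Intervention Quality Assurance and Implementation Measures already treats attendance as an acceptability measure. The label is nevertheless explicit in two places, and an analysis that follows it has no randomised comparison. That is something the article fixes, not something it leaves out.

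It is also fair that the size is assumed. At r = 0 there is no bias, and the 6% is close to nominal. A model of change from baseline removes part of the prognostic difference, so r should be read as the correlation with whatever the model leaves unadjusted. The direction is open as well: clinical need and session payments point away from the idea that better-off families attend more.

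A reader might infer that the plan judges subgroups by fitting each one alone and comparing significance. The text does not support that. The sentence follows the structural equation modelling steps, so separate may only mean separate from those models, and no rule comparing p-values is stated. The 50% figure describes that unstated rule and is no estimate for this trial.

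Nor does the article support saying that Aim 2 would steer who is offered the package. The Discussion rests the choice of package on individual and combined component effects, and no targeting rule is given.

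**Conclusion.** The classification of adherence and sessions attended as moderators is wrong for variables recorded after randomisation that exist only where a component is on. Analysed as written, they can produce false effect modification in either direction; it is not certain that they will. The illustrative false-finding rates of 6%, 19% and 58% at correlations of 0, 0.1 and 0.2 rest on the assumed correlation, the median split, a single follow-up outcome and no family clustering. They show sensitivity to a weak association and are not a forecast.

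On baseline subgroups, the supported point is narrower: the wording should be clarified so that a difference in significance cannot be taken for a difference in effect. The problem is confined to Aim 2. The intention-to-treat estimates of Aim 1 do not depend on it.

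**What to change.** 1. Remove adherence and service use from the moderators in the Objectives and Table 2. Report them as implementation measures, or as within-arm dose-response labelled non-randomised and descriptive.
2. Add a complier-average analysis, with assignment as instrument, only for components where the exclusion restriction is stated and plausible. It is doubtful for the economic component, because the US $50 seed deposit and the matched savings have no stated dependence on attending sessions and so could affect outcomes by another route. For the mental health component, the analysis must also allow for the free public services open to families with that component off.
3. For baseline moderators, state that any claim of differential effect rests on the component × moderator × time interaction in the full sample, with subgroup estimates taken from that model. Say what the separate analyses are separate from.

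The cost is revised wording and a modest amount of modelling. Interaction tests have low power (about 29% in the case worked above), which the Discussion already concedes in general terms. Because follow-up is complete and effect analyses are under way, the change should be dated and disclosed as such.
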